### Outcomes

The primary outcome of the study is executive function (verbal fluency subtype), assessed by the Controlled Oral Word Association Test (COWAT; total F-A-S score), which captures aspects of inhibitory control, cognitive flexibility, and verbal initiation. The primary endpoint is the post-intervention time point. The primary analysis will focus on between-group differences at post-intervention, with additional longitudinal analyses examining changes from baseline and the maintenance of effects at follow-up (12 weeks after the end of the intervention).

The secondary outcomes of the study will be presented as group means and include:

Cognitive function, which will be assessed at baseline, post-intervention, and at the 12-week follow-up after the end of the intervention time points:Attention span and short-term memory, measured by the Digit Span Test – Forward (DST–F);Processing speed and visual attention, measured by the Trail Making Test – part A (TMT–A);Executive function (set-shifting ability), measured by the Trail Making Test – part B (TMT–B);Self-perceived cognitive failures, measured by the Cognitive Failures Questionnaire (CFQ).

Physical Function, which will be assessed at baseline and post-intervention time points:Aerobic fitness, measured by the 6-min Walk Test (6MWT);Lower limb strength, measured by performance in the 30-s Chair Stand Test;Upper limb strength, measured by performance in the Arm Curl Test;Lower limb flexibility, measured by the Sit-and-Reach Test (Wells Bench);Agility and dynamic balance, measured by performance in the Timed Up and Go (TUG) Test;Dual-task performance, measured using the TUG combined with a simultaneous cognitive task.

Cardiovascular parameters, which will be assessed at baseline and post-intervention time points:Office blood pressure, measured using a calibrated and automated oscillometric device;Heart rate variability, measured using a heart rate monitor;Blood pressure reactivity, measured using the auscultatory method during the Stroop Test for 3 min;Heart rate reactivity, measured using a heart rate monitor during the Stroop Test for 3 min.

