### Sample size

The sample size was calculated using G*Power 3.1 software, based on the study’s primary outcome, assessed by the COWAT, using unpublished data from our laboratory. An effect size of ƒ = 0.180 was used, with 90% power and an alpha of 5%. The calculation indicated a required sample of 84 participants, with an additional 20% added to account for potential dropouts, resulting in 102 participants to be recruited.

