### Statistical methods

Descriptive data will be presented as means with standard deviations and/or 95% confidence intervals, or as absolute or relative frequencies, when applicable. Generalized Estimating Equations (GEE) will be used to compare primary and secondary outcomes, assuming an unstructured working correlation matrix. In all GEE models, group and time will be treated as categorical variables, and group × time interactions will be included to test intervention effects. Bonferroni-adjusted post hoc tests will be applied when multiple comparisons are performed. The efficacy of the trial will be assessed using a single pre-specified primary outcome and a single primary comparison, consistent with SPIRIT recommendations for clinical trial protocols. Therefore, no multiplicity adjustment across outcomes will be applied. Analyses of secondary outcomes will be considered exploratory, and multiplicity adjustments will be applied only for multiple comparisons within the same outcome (e.g., Bonferroni-adjusted post hoc tests).

Both per-protocol (PP) and intention-to-treat (ITT) analyses will be conducted. In the analysis following the ITT principle, all randomized participants are analyzed in the group to which they were initially assigned, regardless of adherence, treatment receipt, or protocol deviations. Multiple imputations will be used to impute missing data using a specific function on SPSS software. Additionally, PP analyses will be performed to evaluate the robustness of the findings and the effect of adherence to the intervention. Therefore, participants must have at least 70% attendance during the 12-week intervention to be included in the PP analysis. This threshold was defined to ensure sufficient exposure to the training stimulus to plausibly induce adaptations, while accounting for the variability in attendance commonly observed in exercise interventions involving older adults. This cutoff has been adopted in previous aquatic exercise intervention studies conducted by our research group involving older populations under similar conditions [22].

No additional analyses, such as subgroup or sensitivity analyses, are planned for this trial. All statistical procedures will be performed in the SPSS vs. 28.0 program, and the significance level adopted is α = 0.05. Additionally, between-group effect sizes will be calculated using Cohen's d based on change scores and classified as small (≥ 0.2), moderate (≥ 0.5), or large (≥ 0.8) [60, 61].

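### Plain Bonferroni on the three arm contrasts gives up power that a step-down test for three arms keeps at the same 5% family-wise error, and the family is bounded only by the outcome

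*Protocol article*

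**What the plan says.** The Statistical methods section fits GEE models with group, time and their interaction, and states that "Bonferroni-adjusted post hoc tests will be applied when multiple comparisons are performed". Efficacy is to rest on one pre-specified outcome and one primary comparison, with no adjustment across outcomes; the pair of arms is not named. Secondary outcomes are called exploratory, and for them "multiplicity adjustments will be applied only for multiple comparisons within the same outcome", with Bonferroni post hoc tests as the example. For the analysis, "the significance level adopted is α = 0.05".

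The Outcomes section directs the primary analysis to between-group differences at post-intervention and treats longitudinal analyses as additional. The number of visits differs by outcome. Among the secondary outcomes, "Cognitive function, which will be assessed at baseline, post-intervention, and at the 12-week follow-up" (COWAT, the primary outcome, has the same three time points), while physical, cardiovascular and psychosocial outcomes have baseline and post-intervention only.

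All three arm pairs carry a stated hypothesis at the end of the Background: each programme against control, and combined against conventional.

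**The concern.** Two things follow from the text.

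- **The family has no stated size.** It is limited to one outcome, but a three-arm, three-visit outcome offers several counts: three arm contrasts at one visit, nine across visits, or 36 pairs of group-by-time cells. The same post-intervention contrast could be judged at 0.0167, 0.0056 or 0.0014, and nothing in the text settles which before the data are seen.
- **The method is less efficient than it need be, whichever count is meant.** With exactly three arms, if one pair truly differs, at most one of the other two equalities can still be true. Once one pair has been shown to differ, the other two can therefore each be tested at 0.05. Plain Bonferroni ignores this and holds all three at 0.05/3.

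At stake is the chance of detecting real differences between arms in a trial with about 28 to 34 women per arm.

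**Working it through.** **Inputs from the protocol.** Three arms, 1:1:1; alpha 0.05. Sample size: "An effect size of ƒ = 0.180 was used" with 90% power; "The calculation indicated a required sample of 84 participants" (28 per arm), "with an additional 20% added to account for potential dropouts, resulting in 102 participants to be recruited" (34 per arm).

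**The plan's own figure.** The noncentral F for a group-by-time interaction, with k = 3 arms, m = 3 visits and an assumed correlation ρ = 0.5 with sphericity:

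- λ = f²·N·m/(1−ρ) = 0.0324 × 84 × 3/0.5 = 16.33
- df = (k−1)(m−1) = 4 and (N−k)(m−1) = 162
- power = 90.9%. The smallest N reaching 90% is 82, which becomes 84 for equal arms.

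The 84 is reproduced under these assumptions. The 90% then belongs to an omnibus interaction test and not to any arm contrast. f = 0.18 cannot be turned into a pairwise difference without the mean pattern and correlation, so the pairwise effects below are assumptions (0.4 and 0.8 SD).

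**Counting possible families.**

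| Outcome type | Cells | Arm contrasts at one visit | Arm contrasts, all visits | All cell pairs |
|---|---|---|---|---|
| Three visits | 9 | 3 | 9 | 9×8/2 = 36 |
| Two visits | 6 | 3 | 6 | 6×5/2 = 15 |

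**Single-contrast power under Bonferroni.** Two-sided pooled t test, df = 3n−3, noncentrality d√(n/2). At n = 28 and d = 0.8 the noncentrality is 0.8 × √14 = 2.993.

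| Level | Power, n = 28 | Power, n = 34 |
|---|---|---|
| 0.05 (unadjusted) | 84.1% | 90.4% |
| 0.05/3 | 70.8% | 80.4% |
| 0.05/9 | 55.9% | 67.8% |
| 0.05/36 | 38.3% | 50.7% |

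**Shaffer's rule against Bonferroni with the family of three.** Compare the smallest p-value with 0.05/3; if it is significant, compare the other two with 0.05 each. Simulation with normal data and equal variances; means in the order combined, conventional, control:

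| Means (SD) | Contrast | Bonferroni-3 → Shaffer, n = 28 | n = 34 |
|---|---|---|---|
| 0.8, 0.8, 0 | each exercise arm vs control | 71% → 78% | 80% → 87% |
| 0.8, 0.4, 0 | combined vs conventional | 18% → 29% | 22% → 36% |
| 0.8, 0.4, 0 | conventional vs control | 18% → 29–30% | 22% → 36% |
| 0.8, 0.4, 0 | combined vs control | 71% → 72% | 80% → 82% |

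**Family-wise error.** With all means equal, both rules give about 4.3% to 4.4%, because both start at 0.05/3. When one arm differs by 0.8 SD, Shaffer gives 4.9% to 5.0% and Bonferroni-3 about 1.7%. Shaffer uses the allowed 5%; Bonferroni leaves part of it unused.

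**The case against.** Several objections are fair.

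- **The text does not pool arm and time contrasts.** A reader might infer from the wording about the same outcome that Bonferroni runs over every contrast of that outcome. The documents do not support this. The phrase is set against adjustment across outcomes, and the Outcomes section points to between-group differences at post-intervention. Three contrasts per time point fit the text equally well. The 38% and 56% powers for families of 36 and 9 are therefore worst cases, not what the plan prescribes.
- **The sentence on adjustment within an outcome concerns exploratory secondary outcomes.** This stands. It is the general Bonferroni sentence that reaches the primary outcome, and only when several comparisons are made.
- **A single primary comparison needs no adjustment.** This also stands. At 28 per arm and 0.8 SD, an unadjusted test has 84% power against 78% under Shaffer, so the step-down rule must not be imposed on that comparison.
- **Combined versus conventional is not singled out.** A reader might think that it loses most. With means 0.8, 0.4, 0 the two 0.4 SD contrasts lose equally.
- **Bonferroni is valid and conventional.** True, and it allows simultaneous intervals. When one arm differs, its actual error is also lower (about 1.7%), though still as part of a 5% procedure.

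What remains is an efficiency gain of about 7 points for the 0.8 SD contrasts (when the other two arms are equal) and about 11 to 14 points for the 0.4 SD contrasts. The 0.4 SD contrasts stay poorly powered either way.

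**Conclusion.** The point holds as a loss of efficiency with an unsettled family. Plain Bonferroni is the named method. With three arms, Shaffer's rule rejects whatever Bonferroni over three contrasts rejects, and sometimes more, at the same 5% family-wise limit. The type I error is not at fault. Wider families would lose more, but only if the analysts used them.

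The logic of the rule does not depend on effect size. The sizes do: they rest on assumed means, normal data with equal variances, and a single-visit comparison. The planned GEE on repeated measures could have different absolute power. The 0.8 SD effect is the protocol's own threshold for a large effect.

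**What to change.** Replace the post hoc wording in Statistical methods with text such as:

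> *Apart from the single primary comparison, which is tested at 0.05 without adjustment, the family for each outcome is the three between-arm contrasts at post-intervention and, separately, the three at follow-up for cognitive outcomes; error is controlled per outcome and time point. Within a family the smallest p-value is compared with 0.05/3; if it is significant, the other two are each compared with 0.05 (Shaffer). Within-arm changes and baseline differences are described and do not enter the family.*

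Three points go with it.

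- The exemption needs the primary pair to be named. If no single pair is primary, Shaffer's rule applies to the primary outcome too. If one is named, say how the other two COWAT contrasts at post-intervention are handled. One option is to test each at 0.05 only after the primary pair is significant; the three-arm argument above keeps the error at 5%.
- Separate families for post-intervention and follow-up control error at each time point only. Over both, the error for one cognitive outcome can approach 10%.
- The 4-df group-by-time test should not replace the gate. If it rejected because of follow-up alone, three unadjusted post-intervention contrasts would carry about 12% family-wise error.

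The cost is a few sentences and a calculation by hand from three p-values, with no extra participants, visits or software. The downside is that simple simultaneous confidence intervals are lost. Unadjusted 95% intervals should be labelled as such, because at least one may exclude zero where the step-down test does not reject. At 28 per arm this happened in about 13% of simulated trials with means 0.8, 0.4, 0 and 9% with means 0.8, 0.8, 0.

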### Interventions and comparator

Participants will be randomized into one of three groups: an aquatic aerobic exercise program combined with cognitive tasks, a conventional aquatic aerobic exercise program, or a control group. Aquatic exercises will be standardized as exclusively aerobic due to their demonstrated effectiveness in improving physical function within the proposed 12-week period, as reported in previous studies [20, 21, 23–25]. Accordingly, both intervention groups will perform the same aquatic aerobic exercise program, while the group including cognitive tasks will receive this additional component, which is expected to account for potential differences between the groups. Participants allocated to the control group will not engage in any structured physical or cognitive interventions during the 12-week period. This design will allow us to determine whether any observed improvements in the intervention groups can be attributed to the exercise programs and their inherent characteristics, including the potential contribution of attention and social interaction effects associated with supervised group-based activities, rather than to external factors.

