#### Aquatic exercise intervention groups

The intervention will take place at the thermal pool of Brilhante Club in Pelotas. The pool water temperature will be maintained between 30 and 32 °C, with participants immersed to a depth level between the xiphoid process and the shoulders. Participants in both exercise groups will undertake a 12-week exercise program, consisting of two weekly sessions on non-consecutive days. Each session will last 45 min, comprising a 5-min warm-up, 35 min of aerobic exercises, and a 5-min cool-down and stretching. The group with cognitive tasks will perform this additional component during the main part of the exercises. Both exercise groups will undergo one familiarization session with aquatic exercises and learn to use the Borg’s 6–20 rating of perceived exertion (RPE) scale before the start of the intervention. The exercise sessions will be conducted in groups of 8 to 12 participants and delivered by a physical education professional with a bachelor’s degree ([name]) and expertise in aquatic exercise prescription, under the supervision of the principal investigator ([name]). A second instructor will provide in-pool assistance throughout the sessions.

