#### Control group

The control group will be instructed to maintain their usual physical activity habits and cognitive routines.

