##### Adherence assessments

Attendance will be monitored through the session’s frequency recording and expressed as the percentage of intervention sessions experienced by a participant, given the total number of scheduled sessions.

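### The 70% attendance rule for the per-protocol set has no meaning for controls; on its likelier reading it compares attendance-selected exercisers with unselected controls, which shows neither robustness nor the effect of adherence.

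*Protocol article*

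**What the plan says.** Statistical methods gives one entry rule for the per-protocol set: "participants must have at least 70% attendance during the 12-week intervention to be included in the PP analysis". The reason follows: "This threshold was defined to ensure sufficient exposure to the training stimulus". The purpose is also stated: "PP analyses will be performed to evaluate the robustness of the findings and the effect of adherence to the intervention". The same section plans an ITT analysis of everyone randomised, with multiple imputation, and rules out any further subgroup or sensitivity analysis.

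Adherence assessments defines attendance as a figure "expressed as the percentage of intervention sessions experienced by a participant, given the total number of scheduled sessions". The exercise programme runs for 12 weeks, "consisting of two weekly sessions on non-consecutive days". On the third arm, Interventions and comparator says: "Participants allocated to the control group will not engage in any structured physical or cognitive interventions during the 12-week period". The Control group section adds: "The control group will be instructed to maintain their usual physical activity habits and cognitive routines".

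The Open science section says that the statistical analysis plan is contained in this article, so the rule is not left to another document.

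**The concern.** The rule is written for participants in general, but its yardstick exists in only two of the three arms. The protocol does not say how a control enters the per-protocol set, so the analyst must choose.

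The choice matters because of what the analysis is for. Attendance is known only after randomisation and may go with health, motivation or function. Filtering the exercise arms on it, with no counterpart filter in the control arm, gives up the balance that randomisation provided. If the per-protocol and ITT results against control agree, the agreement may partly reflect selection. If they differ, the difference may be selection rather than adherence. This is also the only supplementary analysis planned, so nothing else would separate the two explanations.

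**Working it through.** **Who can meet the rule**

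- Exercise arms: 2 sessions × 12 weeks = 24 sessions. 70% of 24 is 16.8. 16/24 = 66.7% fails and 17/24 = 70.8% passes, so at least 17 sessions are needed.
- Control arm: 0 sessions scheduled. Attendance is 0/0 (undefined) or is counted as 0%; either way it is not at least 70%.
- Arm size: 102 randomised 1:1:1 gives 34 per arm.

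**Two readings**

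| Reading | Exercise arms | Control arm | Contrasts with control |
|---|---|---|---|
| Literal: all participants | attenders of 17 or more sessions | 0 of 34 | none possible |
| By its rationale: exercise arms only | attenders of 17 or more sessions | all 34 | selected versus unselected |

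The rationale (exposure to training) and the definition of attendance (share of scheduled sessions) both favour the second row.

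**Illustration of the second row**

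The document gives neither the share of women who will miss the threshold nor the link between attendance and COWAT. Both are assumed here. Suppose that there is no true effect, that attendance tendency and outcome are bivariate normal with correlation r, that the outcome SD is 1, and that the lowest share p of attenders is excluded. The exercise-arm mean then shifts by

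shift = r × φ(z) / (1 − p), where z is the p-th quantile of the standard normal.

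- p = 0.20: φ(z)/(1 − p) = 0.280/0.80 = 0.350
- p = 0.30: φ(z)/(1 − p) = 0.348/0.70 = 0.497

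| r (assumed) | p = 0.20 (about 27 of 34 kept) | p = 0.30 (about 24 of 34 kept) |
|---|---|---|
| 0 | 0 | 0 |
| 0.1 | 0.035 SD | 0.050 SD |
| 0.2 | 0.070 SD | 0.099 SD |
| 0.3 | 0.105 SD | 0.149 SD |
| 0.4 | 0.140 SD | 0.199 SD |

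At r = 0.3, a two-sided 5% test of one exercise arm against 34 controls would reject in about 6.9% (p = 0.20) or 8.6% (p = 0.30) of trials with no true effect. A negative r reverses the sign of the shift.

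**Level or change**

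The table applies to the post-intervention level, on which the Outcomes section centres the primary analysis. For change from baseline, which underlies the group × time test and the planned Cohen's d, only the link between attendance and change counts. If attendance relates to a stable trait that raises COWAT equally before and after, that part cancels.

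**The case against.** The strongest reply is that the sense of the rule is plain. It is justified by training exposure and measured against scheduled sessions, so it concerns women who had sessions. What then remains is the familiar limit of any per-protocol comparison with an untreated arm, offered in addition to an ITT analysis of all randomised women. Those who withdraw are still invited to assessment, and the contrast between combined and conventional exercise, on which the Background rests its case, uses the same rule in both arms.

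Much of this stands. A reader might infer that the per-protocol analysis will contain no controls; the stated rationale makes that an unlikely intention. A reader might also infer that the bias must favour exercise. That needs a positive correlation, which is plausible but appears nowhere in the document. Nor can the shift be set against a planned effect in SD units: the Sample size section gives f = 0.180 without saying to which test it belongs, and the SD difference it implies depends on that.

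The reply does not supply a rule for controls. Nor does it answer the difficulty that a one-sided selection is assigned two tasks it cannot perform, with no other analysis planned to help.

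**Conclusion.** The concern holds in limited form. As written, the rule is undefined for one arm. On its likelier reading, the per-protocol contrasts with control are non-randomised and cannot alone show robustness or the effect of adherence. The illustrative 0.04 to 0.20 SD rests wholly on the assumed r of 0.1 to 0.4 and exclusion of 20% to 30%; with r = 0 there is no shift. The direction is not established.

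The ITT results are untouched. The missing control criterion does not affect the combined-versus-conventional contrast, although that contrast too selects on behaviour after randomisation. The point therefore bears on how the supplementary analysis is defined and read, not on the validity of the trial's main analysis. It should be corrected before the data are analysed.

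**What to change.** 1. State that the 70% rule applies to the two exercise arms and that all assessed controls are kept. Do not exclude controls on the activity questionnaire. It counts leisure activity lasting more than 15 min, so it cannot apply the eligibility definition of regular exercise (at least 20 min on two or more days a week), and it does not record cognitive training. Removing active controls would also add a second selection after randomisation.
2. Adjust the per-protocol models for baseline COWAT, age and MMSE, all already collected. This reduces imbalance on those measures but not on unmeasured ones.
3. For each exercise arm against control, estimate the effect of adherence with randomisation as the instrument and sessions attended (controls = 0), or any attendance, as the exposure. In its simplest form this is the ITT difference divided by the between-arm difference in mean exposure. Do not use the 70% cut as the exposure, because that would assume that 1 to 16 sessions have no effect. Label the estimate supportive.
4. State that ITT carries the conclusion and that per-protocol results against control are non-randomised and supportive.

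The cost is some rewording and one extra analysis on data already being collected. The instrumental-variable estimate has a wider interval. It assumes that allocation acts only through attendance and, with sessions as the exposure, that the effect is linear in the number attended.
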